## Abstract

Background/Objectives: Pediatric obstructive sleep apnea (OSA) is a prevalent medical condition, affecting 1–5% of non-syndromic children and 30–90% of children with Down syndrome. Given the severity of the condition and the associated health risks, early and effective treatment is crucial. However, current treatment modalities are often invasive or suffer from poor patient adherence. Additionally, adenotonsillectomy, the first-line treatment in pediatric OSA, seems not to be effective in every child, leaving children with residual OSA postoperatively. These challenges are particularly pronounced in high-risk populations, such as children with Down syndrome, highlighting the need for alternative therapeutic strategies. Therefore, a protocol is presented to evaluate the effectiveness of orofacial myofunctional therapy (OMT) as a treatment for OSA in two pediatric populations: (1) Non-syndromic children aged 4–18 years: 10 weeks of OMT. (2) Children with Down syndrome aged 4–18 years: 20 weeks of OMT. Effects of the OMT program will be evaluated on: sleep parameters (e.g., obstructive Apnea–Hyponea Index (oAHI), snoring frequency); orofacial functions (e.g., breathing pattern, tongue position at rest); quality of life outcomes. Methods: A pretest–posttest design will be used to evaluate the effectiveness of OMT in both children with and without Down syndrome and OSA. Both objective measures and patient-reported outcomes are being collected. Results: OMT is expected to improve orofacial functions, reduce OSA severity and symptoms, and enhance quality of life in both non-syndromic and syndromic children. Conclusions: This multidisciplinary research protocol, involving collaboration between ENT specialists and speech-language pathologists, aims to provide a comprehensive understanding of the potential benefits of OMT in treating OSA.

## 1. Introduction

### 1.1. Epidemiology and Therapeutic Challenges in Pediatric OSA

Obstructive Sleep Apnea (OSA) is a prevalent medical condition with a prevalence of 1% to 5% in otherwise healthy, non-syndromic children and 30% to 90% in children with Down syndrome [1,2]. OSA is classified under sleep breathing disorders and characterized by repeated episodes of upper airway (UA) obstruction due to UA collapse during sleep, with complete (apnea) or partial (hypopnea) interruption of airflow resulting in abnormal ventilation, abnormal breathing, and sleep disturbance [3]. The UA collapses are a result of increased UA collapsibility, anatomic narrowing of the UA, or both [1]. The underlying cause of pediatric OSA is considered multifactorial. Factors such as adenoid and tonsil hypertrophy, obesity, anatomical or neuromuscular deficits, and hypotonic neuromuscular disorders can be involved, leading to multilevel obstruction of the UA during sleep [4].

Among these factors, adenoid and tonsil hypertrophy is the most commonly reported cause of OSA in children, making adenotonsillectomy (AT) the standard therapeutic approach [4]. However, 20% of otherwise healthy, typically developing children suffer from residual OSA after AT [5]. The persistence of OSA post-AT can be attributed to the multifactorial etiology of OSA, suggesting that AT alone may not adequately address all underlying causes of airway obstruction. In children with Down syndrome, this challenge is even more pronounced. Despite undergoing AT, up to 55% of children with Down syndrome continue to experience residual OSA [2]. This high rate is due to the complex interplay of anatomical and functional predisposing factors for OSA in this population, including macroglossia, generalized hypotonia, mouth breathing, and narrow upper airways resulting from craniofacial abnormalities. These features contribute to increased UA collapsibility and multilevel obstructions, often limiting the effectiveness of single-treatment approaches such as AT [6,7,8].

Other treatment options for pediatric OSA include continuous positive airway pressure (CPAP) and rapid maxillary expansion (RME). These treatments also show several drawbacks in children, such as low adherence to CPAP and impaired facial growth due to wearing the mask and chin strap [4,9]. Furthermore, Guilleminault et al. [10] reported persistence or recurrence of OSA in nearly 65% of non-syndromic and non-overweight children several years after AT and RME. In children with Down syndrome, surgical procedures such as genioglossus advancement, lingual tonsillectomy, and tongue base volume reduction are described to reduce OSA [11]. However, many of these studies report a significant decrease in OSA post-surgery, but the Apnea–Hypopnea Index (AHI) still reveals severe residual OSA after intervention [12,13,14].

Untreated or inadequately treated OSA can lead to behavioral problems, school problems, hyperactivity, nocturnal enuresis, sleep terrors, insomnia, depression, and other psychiatric problems [3,4]. Compared to non-syndromic children, children with Down syndrome may be even more vulnerable to these effects of OSA [11]. The high prevalence of residual OSA post-AT and the negative impact of residual OSA on the overall health, highlight the importance of exploring new therapeutic modalities to treat OSA in children with and without Down syndrome.

### 1.2. Orofacial Myofunctional Disorders and Therapy in OSA

Recent research shows that orofacial myofunctional disorders (OMDs) such as mouth breathing, caudal tongue positioning, and genioglossus dysfunctions occur in patients with OSA [10,10,15]. These OMDs increase UA collapsibility and can therefore be associated with the occurrence of UA collapses and OSA [16]. One of the OMDs most frequently associated with OSA is mouth breathing [17]. Adenoid and tonsil hypertrophy, the main cause of pediatric OSA, narrows the nasopharynx and oropharynx [18]. If nasal resistance exceeds a certain level, a shift to mouth breathing occurs [19]. After removal of the obstructive tissue, more than half of the children maintain the habit of mouth breathing, which in turn is associated with the development of skeletal disorders, inflammation of pharyngeal tissues, and recurrence of OSA in the long term [10,10]. Lee, Guilleminault, Chiu, and Sullivan [10] found that non-syndromic children who were cured from OSA after AT but remained breathing through their mouth during the night showed a recurrence of OSA 12 months postoperatively. In addition, a significantly higher OSA severity post-AT (range 12–72 months) was found in children who did not undergo orofacial myofunctional therapy (OMT) post-AT compared to children who did undergo OMT post-AT to reduce mouth breathing [10,10].

Fitzpatrick, McLean, Urton, Tan, O’Donnell and Driver [16] explained the relationship between mouth breathing and OSA by stating that when the child opens the mouth during sleep, the tongue and the jaw make a posterior inferior movement. This movement results in a reduction in retroglossal and retropalatal diameter of the upper airway and prevents forceful contraction of the upper airway dilating muscles, which increases upper airway collapsibility and subsequently the frequency of OSA [20]. In addition, mouth breathing leads to a deactivation of nasal receptors, resulting in reduced maintenance of spontaneous ventilation and apneas [21]. Furthermore, the amount of nitric oxide (NO) released in the nose and paranasal sinuses, is decreased during mouth breathing. NO plays an important role in blood oxygenation and the maintenance of airway patency. Consequently, NO deficits induce upper airway collapsibility and OSA [22].

Other OMDs observed in patients with OSA are dysfunctions of intrinsic and extrinsic tongue muscles, such as the genioglossus muscle (GG) [10,15,23]. The GG is the main upper airway dilator muscle and is responsible for moving the tongue anteriorly, dilatating the oropharynx, and preventing upper airway obstruction [24,25]. A decreased ability of the GG to maintain airway patency during sleep causes repetitive upper airway closure [26]. Results of an electromyography study showed significantly greater GG activity during wakefulness and a greater decline of GG activity during sleep onset in non-syndromic children with OSA, indicating increased upper airway collapsibility [15]. Furthermore, one adult study found a significantly negative correlation between tongue protrusion strength and OSA severity (apnea-index). Kanezaki et al. [27] concluded that a higher tongue protrusion strength is associated with increased upper airway stabilization. No studies regarding tongue protrusion strength in children with OSA are available. However, one study examined upward tongue strength in 78 children with OSA, showing a significantly lower tongue strength in children with OSA compared to children without OSA [23].

Given the association between OMDs and OSA, OMT is emerging as a promising treatment for pediatric OSA in addition to or as a replacement for structural treatments such as AT [28]. OMT is a therapeutic method for neuromuscular rehabilitation programs consisting of a series of isotonic and isometric exercises, designed to enhance sensitivity, proprioception, mobility, coordination, and strength of the oropharyngeal structures involved in breathing, mastication, swallowing, and speech. Respiratory muscle training may be included as part of the therapy, aiming to strengthen pharyngeal, diaphragmatic, external intercostal, and accessory respiratory muscles. In patients with OSA, OMT aims to improve muscle resistance, balance the contraction of pharyngeal muscles, and correct abnormal functional and resting postures of the oropharyngeal structures in order to stabilize the upper airway during sleep [29,30].

Only a few small studies examined the effect of OMT as a secondary treatment for OSA in non-syndromic children after AT [10,10,31,32]. In these studies, OMT focused on the elimination of mouth breathing, the correction of tongue posture, and increasing tongue strength [31,32]. The results showed a significantly lower AHI, reflecting a decrease in OSA severity, in the groups that followed OMT [10,10,31,32]. However, the available literature about OMT as a secondary treatment for pediatric OSA is limited, and there is a lack of high-quality evidence. Studies show methodological limitations such as small sample sizes, non-standardized therapy methods, and limited outcome measurements [33]. Additionally, no studies examined the effect of OMT as primary treatment for pediatric OSA. When looking specifically at studies in children with Down syndrome, only one study investigated the effect of one week of OMT on OSA in this population [2]. Results showed a slight to negligible decrease in OSA, which is expected after only one week of therapy. No research is available regarding the effectiveness of long-term OMT on OSA in children with Down syndrome. Nevertheless, there is a major need for an alternative treatment to optimize health conditions and quality of life in this population [34].

## 2. Materials and Methods

### 2.1. Participants

#### 2.1.1. Non-Syndromic Children

Children with OSA will be recruited via the Pediatric Sleep Center, the Otorhinolaryngology and the Pneumology department of Ghent University Hospital. They will be selected to participate in the study based on the inclusion criteria: aged between 4 and 18 years, diagnosed with OSA confirmed by an oAHI > 1 on polysomnography. The lower age limit is chosen because a certain level of maturity is required before a child is capable to understand and perform OMT exercises [10]. Exclusion criteria are: history of OMT, orthodontic treatment in progress, other OSA treatments in progress, orofacial congenital deformities, nasal congestion, intellectual disability and obesity (>2 SD above P50). Both children with and without previous surgical removal of adenoids and/or tonsils will be included. Inclusion and exclusion criteria will be assessed through a questionnaire and an ENT examination.

#### 2.1.2. Children with Down Syndrome

Children with Down syndrome will be recruited via the Pediatric Sleep Center, the department of otorhinolaryngology, and the Down Clinic at Ghent University Hospital. They will be selected based on the inclusion criteria: aged between 4 and 18 years, diagnosis of Down syndrome (trisomy 21), diagnosis of residual OSA after adenoidectomy and/or tonsillectomy confirmed by polysomnography (oAHI >1). Exclusion criteria are: nasal congestion, inability to close the mouth and bring the tongue inside the dental arch, presence of other neuromuscular, craniofacial, and/or genetic disabilities, history of OMT, orthodontic treatment in progress, and other OSA treatments in progress. Inclusion and exclusion criteria will be assessed through a questionnaire and an ENT examination.

### 2.2. Sample Size

Based on a study of Villa, Evangelisti, Martella, Barreto and Del Pozzo [32], a sample size of *n* = 23 was calculated for the pretest–posttest study in non-syndromic children (G*Power, McNemar test, 2-sided). Calculation was based on the outcome ‘oral breathing’ with an α level of 0.005 (to account for multiple testing), a power of 0.80, and a decrease of 66.7% (12/18) in the proportion of children exhibiting oral breathing post-intervention. Taking into account a dropout rate of 15%, *n* = 27 will be the target in the study. For the pretest–posttest study in children with Down syndrome, sample size calculation is not yet possible given the innovative nature of this objective.

### 2.3. Design

Two separate pretest–posttest studies will be conducted to determine the effects of OMT in the management of pediatric OSA in non-syndromic children (pretest–posttest study 1) and children with Down syndrome (pretest–posttest study 2). Intervention will consist of a 10-week OMT in non-syndromic children and a 20-week OMT in children with Down syndrome [35]. Both studies include 2 measurement moments: (1) at the start of the study (baseline), and (2) after the therapy period. All measurement moments consist of an evaluation of orofacial myofunctional, sleep, and quality of life outcomes. To avoid observer bias, all assessments will be performed blindly, so assessors will be blinded to group allocation and study phase.

To reduce the number of therapy sessions and investigations in these children, no sham therapy will be used. Because of the complexity of OSA and the variability in patients within the objective, it is chosen not to compare the results against a control group but to look at performance at an individual level.

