### 2.7. Sleep Assessment

#### 2.7.1. Screening for Pediatric Sleep Disorders

The Sleep Disturbance Scale for Children (SDSC) is a validated, parent-reported questionnaire to assess the presence of sleep disorders in children. Comprising 26 items on a 5-point Likert scale, the SDSC evaluates sleep disorders on six domains: disorders of initiating and maintaining sleep, sleep disordered breathing, disorders of arousal, sleep–wake transition disorders, disorders of excessive somnolence, and sleep hyperhidrosis [48,49]. Different types of sleep disorders can co-occur and symptoms can overlap among various pediatric sleep disorders. Therefore, it is important understand the child’s overall sleep health and identify potential co-occurring sleep disorders that may affect treatment outcomes.

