#### 2.7.2. OSA Severity and Symptoms

All children will undergo a full-night laboratory polysomnography (PSG). The PSG will be performed and scored according to the standard criteria of the American Academy of Sleep Medicine by specialists from the Pediatric Sleep Center [46,47,50]. Electroencephalogram (EEG), chin electromyogram (EMG), and electrooculogram tracings will be used to determine sleep stage. In addition, PSG will provide data regarding respiratory events by measuring abdominal movements with strain gauges, oronasal airflow with an oronasal thermal sensor and nasal pressure transducer, and oxygen saturation with pulse oximetry. Snoring sounds will be detected by a snore microphone, and limb movements will be recorded using EMG [28,50]. PSG will objectively evaluate OSA severity (i.e., AHI, Arousal Index, Oxygen Desaturation Index, sleep efficiency) and OSA symptoms (i.e., snoring frequency). PSG results will be processed and interpreted by an expert at the Pediatric Sleep Center.

The Pediatric Sleep Questionnaire (PSQ) will be completed by the child’s parents to evaluate OSA symptoms. Twenty-two items within the following domains: snoring, observed apnea, daytime fatigue, and OSA-related behavioral disturbances will be scored on a dichotomous scale (present/absent). The variable obstructive Sleep-Related Breathing Disorder score (SRBD score) will be derived from the questionnaire by calculating the average of the non-missing items [51]. This questionnaire was proven to be reliable and valid with high sensitivity and specificity [52].

The Child Sleep Habits questionnaire (CSHQ) will be completed by the child’s parents to evaluate sleep disorders in children [53]. Thirty-three items within the following domains: bedtime resistance, sleep-onset delay, sleep duration, sleep anxiety, night wakening, parasomnias, sleep disordered breathing, and daytime sleepiness are rated on a 3-point scale. The CSHQ was proven to be reliable and valid [53].

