#### 2.7.3. Quality of Life Assessment

Sleep-related quality of life evaluation will be performed using the 28-item parent-reported Child Health Questionnaire (CHQ). The CHQ is a valid and reliable tool to assess the impact of OSA on quality of life [54,55].

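### Section 2.3 claims blinding to study phase for all assessments, which cannot hold for the four parent-completed questionnaires, including the only quality-of-life measure

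*Protocol article*

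**What the plan says.** Section 2.3 (Design) describes two separate single-arm before-after studies with measurements at baseline and after the therapy period. It fixes their content: "All measurement moments consist of an evaluation of orofacial myofunctional, sleep, and quality of life outcomes". The next sentence, whose stated aim is to prevent observer bias, says that "all assessments will be performed blindly, so assessors will be blinded to group allocation and study phase". It makes no exception. The same section rules out sham therapy and a control group.

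The later sections name who supplies each measurement:

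- The SDSC (2.7.1) "is a validated, parent-reported questionnaire to assess the presence of sleep disorders in children".
- The PSQ and the CSHQ (2.7.2) are both filled in by the child's parents.
- The CHQ (2.7.3), the only quality-of-life instrument, is also parent-reported.
- For polysomnography (2.7.2), "PSG results will be processed and interpreted by an expert at the Pediatric Sleep Center".
- The orofacial assessment, perceptual and instrumental, is done by two speech-language pathologists who take no part in treatment and are masked with regard to the study's purposes (2.6.1). The OMES is rated blind from video samples put in random order (2.6.2).

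**The concern.** The blinding sentence covers every assessment, and quality of life is listed among the assessments one sentence earlier. Yet several instruments are answered by people who cannot be blind to phase. The sentence also offers blinding to group allocation in studies where nothing is allocated.

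In an uncontrolled before-after study, hiding the phase from whoever rates the outcome is the main protection against ratings drifting in the expected direction. The article hypothesises better sleep quality and overall well-being, and Section 3 assigns daily functioning and well-being to the questionnaires. A reader who takes Section 2.3 at its word would believe that this evidence is protected from expectation, and a results paper could repeat the statement.

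**Working it through.** The point rests on no sample size, power or alpha figure, and the plan gives no figure to reproduce. The check is a count of the instruments used at both measurement moments, by who supplies the rating and whether a step that hides the phase is described. The ENT examination and the demographic questionnaire are left out because they are done only at the start.

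| Instrument | Section | Who supplies the rating | Phase-hiding step described? |
|---|---|---|---|
| OMES | 2.6.1, 2.6.2 | Two speech-language pathologists, from video | Yes: random order, blind rating |
| IOPI | 2.6.1, 2.6.3 | Measured on the child; assessors outside the treatment | No, beyond the general statement and 2.6.1 |
| PSG | 2.7.2 | Sleep Center specialists | No, beyond the general statement |
| SDSC | 2.7.1 | Parent | Not possible |
| PSQ | 2.7.2 | Parent | Not possible |
| CSHQ | 2.7.2 | Parent | Not possible |
| CHQ | 2.7.3 | Parent | Not possible |

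**Count.** Parent-completed: 4 of 7 = 57%. Blindable and covered by the general statement: 3 of 7 = 43%. Of those three, one (OMES) has a described mechanism.

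**Why blinding is not possible for the four.** Section 2.8.1 gives every participant weekly 45-minute sessions and 10 minutes of daily home practice, for 10 weeks or, in Down syndrome, 20 weeks. Appendix A adds lip taping by day and night. With no sham or control, every post-test follows active therapy. A parent therefore knows whether a form is being completed before or after therapy.

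**Group allocation.** All participants receive OMT (2.8.1). The only grouping is Down syndrome status, which is a characteristic of the child and defines two separate studies. There is no allocation from which an assessor could be blinded.

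**By outcome domain.** Quality of life has one instrument (CHQ), so the whole domain lacks the stated protection. In the sleep domain, the three questionnaires lack it and PSG does not. In the orofacial domain, no instrument is parent-reported.

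**Limitations already stated.** Section 3 concedes that, without a control group, the design is open to placebo effects and unmeasured confounding. It does not mention unblinded parent report.

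**The case against.** The strongest reply is that the sentence aims at observer bias and speaks of assessors, so it means professional observers only. Parents are respondents, and the article openly labels their questionnaires as parent-reported. The Abstract separates objective measures from patient-reported outcomes, and Section 3 calls the latter subjective. This reading is possible and makes the error more likely one of wording than of intent. But the sentence says all assessments, directly after naming quality of life among them, and the narrow reading still leaves the reference to group allocation wrong.

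A second reply is that the SDSC sits under a screening heading, with a rationale about co-occurring disorders, so it may not be an effect outcome. Without it the count is 3 of 6 (50%), and the quality-of-life domain is still wholly parent-reported.

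Several stronger readings are tempting, and the documents do not support them:

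- *Parents deliver the home practice.* Section 2.8.1 says that the child repeats the exercises and states no parental role. The point does not need one.
- *IOPI cannot be blinded, making it 5 of 7.* Live measurement does not rule out hiding the phase, and Section 2.6.1 provides assessors outside the treatment. Masking to the study's purposes is not the same as masking to phase, but all that can be said is that no phase-hiding step is described.
- *PSG is scored unblinded.* The general statement covers it and nothing in Section 2.7.2 contradicts it. An article may leave file handling to the full protocol.
- *Phase masking is the only safeguard.* The plan also has objective PSG, instrumental measurement and independent orofacial assessors, and it acknowledges placebo effects.

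**Conclusion.** The universal blinding claim in Section 2.3 is wrong as written. It cannot hold for 4 of the 7 before-after instruments, including the only quality-of-life measure, and blinding to group allocation has no meaning where every child gets the same type of therapy. This rests on one inference that needs little defence: parents know whether their child has been through the therapy period.

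For OMES the claim is supported by a described mechanism. For PSG and IOPI it is achievable and promised, but the means are not given.

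A reader might infer that the study's evidence as a whole is unblinded. That does not follow. The PSG outcomes can be scored blind. So, probably, can oral breathing, the outcome behind the sample size in Section 2.2; that it is rated within OMES is an assumption, because Section 2.2 names no instrument. The error concerns what the questionnaires can support. It should be corrected, but it does not invalidate the design.

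**What to change.** 1. In Section 2.3, limit the blinding statement to the professional assessors: OMES rating from randomised video, PSG scoring from files coded without a visit label, and IOPI measurement by the speech-language pathologists outside the treatment, as far as the phase can be hidden from them.
2. Delete the reference to group allocation.
3. State that the SDSC, PSQ, CSHQ and CHQ are completed by parents who know the phase and are therefore unblinded. Add this to the limitations in Section 3, next to placebo effects.
4. State that a conclusion of effectiveness will not rest on the parent-reported outcomes alone.

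The cost is a few sentences and the coding of PSG files. The drawback is that the questionnaire results, and with them the whole quality-of-life domain, carry less weight in the conclusions.
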